### 2.10. Ethical Consideration

This study was approved by the Institutional Review Board (IRB) of Kongju National University, granted exemption status on 22 July 2024 (No. KNU_2024-07). This study design complies with the Declaration of Helsinki. Before data collection, all study participants will receive information about the study’s purpose, procedures, data collection period, their right to withdraw at any time without penalty, and that their data will be confidential and will be stored in a safe place. All participants will be invited to read an informed consensus and will be assured. Informed consent will be obtained from participants before proceeding with data collection.

All data collected from participants during the study will be treated with utmost confidentiality and privacy, ensuring participant anonymity through the use of unique identifiers; data will be collected only after obtaining prior informed consent. Participants will be guaranteed that study results will be published in an aggregated form, not allowing the identification of participants. Research assistants will be trained to respect participants’ status and time during data collection. If they notice participants becoming tired during data collection, they will offer a pause. If the participant exhibits excessive emotional burden, we will provide tailored interventions and assess whether the participant can continue the program. If the outcome is negative, the data collected up to that critical point will be retained, and the reasons for study withdrawal will be documented accordingly.

Participant data will initially be recorded in a research notebook and subsequently transferred to a secure storage device. All information will be securely stored in a separate, designated location under the supervision of the principal investigator. Collected data will be retained for 5 years after the study’s completion and will be permanently deleted afterward. Electronic files will be password-protected, with the passwords regularly updated to maintain security. Access to personal data will be strictly limited to the principal investigator, co-researchers, evaluators, data managers, and authorized members of the research team.

### 2.11. Data Monitoring

An interim analysis of the measurement data will be conducted 1 week after the intervention to evaluate the effectiveness, validity, and safety of the intervention. To ensure objectivity and minimize bias, this analysis will be performed by an external statistician. If any potential safety concerns are identified during the analysis, the statistician will immediately report the findings to the principal investigator. Thereafter, the principal investigator will carefully review the interim analysis results and make an informed decision on terminating or continuing the study.

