### 1.1. Aims

#### 1.1.1. Primary Objectives

To evaluate the effectiveness of a Health Belief Model (HBM)-based health education program on the number of unintentional home injuries among community-dwelling older adults from baseline to post-intervention and at one-month follow-up.

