### 2.3. Sample Size

Sample size calculation was performed using G*Power 3.1.9.2. (Heinrich-Heine-University, Düsseldorf, Germany) Assuming a medium effect size of 0.25 [24], an alpha level of 0.05, a target statistical power of 0.80, an intraclass correlation coefficient of 0.5 to account for the correlation between repeated measures, two groups, and three measurement timepoints, the minimum required sample size was calculated to be 44 participants (22 per group). To accommodate a potential 20% dropout rate during the intervention period, the study aims to recruit a total of 54 participants, with 27 allocated to the intervention group and 27 to the control group.

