### 2.9. Data Analysis

Data analysis will be performed using SPSS version 26 (IBM Corp., Armonk, NY, USA). Descriptive statistics, including means, medians, frequencies, and percentages, will be used to analyze the general characteristics of the intervention and control groups. Normality of continuous variables will be assessed using the Shapiro–Wilk test. For normally distributed data, the homogeneity of participant characteristics and variables between groups prior to the intervention will be tested using the χ^2^ test, unpaired *t*-test, and one-way analysis of variance. Differences in score changes between the intervention and control groups at the three timepoints—baseline (T0), 1 week after intervention (T1), and 1 month after intervention (T2)—will be analyzed using repeated measures analysis of variance to evaluate between-group differences, within-group differences across the three timepoints, and interactions. For non-normally distributed data, analyses will be conducted using the Mann–Whitney U test and generalized estimating equations. All analyses will follow the intention-to-treat (ITT) principle, including all randomized participants in their originally assigned groups, regardless of adherence or withdrawal. Missing data will be handled using multiple imputation based on the fully conditional specification (FCS) method within SPSS version 26.0. Covariates such as age, sex, and baseline scores will be included to control for potential confounding factors.

To ensure robust statistical evaluation, Type I (alpha) error control will be prioritized, and the Holm–Bonferroni correction will be applied to maintain the overall significance level at *p* < 0.05 (two-tailed). An interim analysis will be descriptive only, focusing on data completeness and participant safety, without formal hypothesis testing to avoid Type I error inflation. Statistical significance will be set at a *p*-value of 0.05. Care will be taken to ensure that all participants complete the program and data collection, minimizing missing data through active follow-up.

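### Sections 2.9 and 2.11 conflict on whether the interim analysis covers effectiveness, and 2.11 does not limit the decision to continue to safety

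*Protocol article*

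**What the plan says.** Two current sections of the protocol article describe the interim analysis.

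- **Section 2.9 (Data Analysis)** restricts it: "An interim analysis will be descriptive only, focusing on data completeness and participant safety, without formal hypothesis testing to avoid Type I error inflation". The same paragraph makes control of alpha a priority and applies Holm–Bonferroni to hold the overall two-sided level at 0.05.
- **Section 2.11 (Data Monitoring)** gives it a wider purpose: "An interim analysis of the measurement data will be conducted 1 week after the intervention to evaluate the effectiveness, validity, and safety of the intervention". An external statistician performs it. The section continues: "If any potential safety concerns are identified during the analysis, the statistician will immediately report the findings to the principal investigator". After that, "the principal investigator will carefully review the interim analysis results and make an informed decision on terminating or continuing the study".

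The primary objective (section 1.1.1) compares injuries "from baseline to post-intervention and at one-month follow-up", so T1 and T2 are both primary assessment times. The sample size (section 2.3) uses "an alpha level of 0.05, a target statistical power of 0.80" and mentions no allowance for an interim look.

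**The concern.** Effectiveness lies outside the stated focus of the interim in section 2.9 and is the first purpose named in section 2.11. A statistician following one section would prepare a different report from a statistician following the other.

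Two things are at stake.

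1. **Continuation.** Section 2.11 attaches the terminate-or-continue decision to the interim results in general. If those results include effectiveness, an informal judgement about benefit, or lack of it, could affect whether T2 is collected. Stopping at T1 would lose the one-month assessment for everyone who had not yet reached it.
2. **Knowledge before T2.** The primary outcome is a count of incidents over the preceding month (section 2.8.1), supported by injury logs that the research team reviews and reinforces (section 4). Sections 2.7.1 and 2.7.2 have the researcher deliver the lectures in both arms. If the study lead learned how the arms compared while T2 was still being collected, that could influence follow-up contact and reporting.

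**Working it through.** **Step 1. The two sections side by side.**

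| Feature | Section 2.9 | Section 2.11 |
|---|---|---|
| Purpose | Completeness and safety | Effectiveness, validity and safety |
| Method | Descriptive, no test | Not stated |
| Reporting to the principal investigator | Not stated | Triggered by safety concerns |
| Decision | None mentioned | Principal investigator terminates or continues after reviewing the interim results |
| Efficacy criterion or alpha allowance | None (no testing) | None |

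The purpose row is a direct mismatch. The decision row is an ambiguity: the only stated trigger for reporting is safety, but what is reviewed is the interim results without qualification.

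**Step 2. Does the interim cost alpha?** No stated figure has to be reproduced here. If 2.11 is read under 2.9's limits (descriptive, no efficacy decision), nothing is spent and the overall level stays at 0.05.

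**Step 3. Size of the worst case.** Suppose instead that the T1 effectiveness look served as a test at two-sided 0.05 with stopping allowed, followed by a final test at 0.05. Let Z1 and Z2 be standard normal under the null with correlation ρ, and c = 1.96. Then

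overall error = 1 − P(|Z1| ≤ c and |Z2| ≤ c).

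For ρ = 0 this is 1 − 0.95² = 0.0975. For other values it comes from the bivariate normal distribution:

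| Assumed ρ | Overall two-sided Type I error |
|---|---|
| 0 | 0.0975 |
| 0.3 | 0.0951 |
| 0.5 | 0.0907 |
| 0.7 | 0.0835 |
| 0.9 | 0.0704 |

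The documents give no correlation between test statistics at the two looks, so ρ is an assumption and the result is a range. The calculation also reduces the final analysis to a single Z-test. The plan is repeated measures ANOVA or generalized estimating equations over T0, T1 and T2, so the figures indicate scale only.

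**Step 4. Can safety and the primary outcome be kept apart?** Section 2.8.1 counts falls, cuts, burns and similar incidents as the primary outcome. Section 2.12 defines an adverse event broadly enough to cover many of the same incidents. A by-arm safety table could therefore reveal the primary comparison even after effectiveness is removed from the interim's purpose.

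**The case against.** The strongest reply is that the sections can be read together: 2.11 says when the look happens, who does it and why, and 2.9 says how, namely without a test. Several parts of this reply stand.

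- A reader might infer that 2.9 says no interim effectiveness analysis will take place. It does not. It bars hypothesis testing and sets a focus, and it does not forbid describing effectiveness data.
- A reader might infer that 2.11 gives the principal investigator power to stop for benefit. No sentence says so. *Thereafter* follows directly on the sentence about safety concerns and may tie the decision to them. The lack of an efficacy boundary fits a plan with no efficacy stopping as well as it fits a gap.
- A reader might infer that the study lead will see results by arm. Section 2.11 does not say whether results are pooled or by arm. It also gives the analysis to an external statistician to limit bias, and section 2.5 provides separate evaluators described as unaware of allocation.
- A reader might take the 7% to 10% as the trial's actual error rate. It is not, because it needs a test at T1 that 2.9 rules out.

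The reply does not remove the mismatch. Even with the decision tied to safety, 2.11 still schedules an evaluation of effectiveness outside 2.9's focus, and its wording does not confine the review or the decision to safety. A fuller protocol might settle this, but the article's own two statements still disagree.

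**Conclusion.** The article is wrong as written: it contradicts itself on the scope of the interim analysis. It leaves open whether effectiveness results may bear on continuation and whether they reach the study lead before T2. This should be fixed, but it does not show that the trial will stop on efficacy or that its Type I error is already inflated.

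The conclusion rests on the text of sections 2.9 and 2.11 and on no calculation. The error range of about 7% to 10% against a planned 5% is conditional on two tests at nominal two-sided 0.05 and an assumed correlation of 0.9 to 0. With a descriptive look and no efficacy decision, the excess is zero.

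**What to change.** Reconcile section 2.11 with section 2.9:

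1. Delete effectiveness from the purpose of the interim analysis in 2.11, and repeat there that the look is descriptive and covers completeness and safety.
2. State that continuation of the study will not be decided on effectiveness results.
3. Keep all by-arm tables, including by-arm counts of home injuries reported as adverse events, with the external statistician until the T2 data are locked.
4. State what safety information is escalated to the principal investigator, and in what form, given that home injuries can count as both outcome and adverse event.

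Items 1 and 2 are edits of a sentence or two. Items 3 and 4 need a short agreed reporting arrangement with the external statistician whom 2.11 already provides for. None of this needs extra participants or data, but it protects the trial only if it is in place before the T1 look.

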### 2.12. Harms

All study participants will be continuously monitored for the occurrence of adverse events (AEs) and serious adverse events (SAEs) throughout the intervention period and the one-month follow-up. An adverse event (AE) is defined as any undesirable or unintended medical occurrence experienced by a participant, regardless of its relationship to the intervention. A serious adverse event (SAE) refers to any event that results in death, is life-threatening, requires hospitalization, or causes persistent disability.

The safety of participants is the top priority of this study, and a systematic approach will be applied to both the implementation and evaluation of the program. Data will be collected at three timepoints: before the intervention, one week after the intervention, and one month after the intervention. All reported events will be systematically recorded in a standardized Excel file. In the event that an unintentional home injury occurs during the study period, participants will be instructed to contact the research team immediately. If a change in a participant’s clinical condition is identified during the intervention or follow-up period that meets the criteria for discontinuation, participation will be terminated immediately to ensure safety. In such cases, participants will be referred for primary care or, if necessary, specialized medical evaluation and follow-up. The research team will conduct additional follow-up to confirm the participant’s recovery and safety status.

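### Discontinuation ends participation rather than only the programme, so post-intervention injury counts may be lost for reasons linked to the primary outcome

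*Protocol article*

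**What the plan says.** Section 2.12 (Harms) covers a change in clinical condition, in the intervention or follow-up period, that satisfies the discontinuation criteria. In that case "participation will be terminated immediately to ensure safety". The criteria are not listed. Referral follows, and then: "The research team will conduct additional follow-up to confirm the participant’s recovery and safety status". Nothing is said about whether the T1 and T2 injury counts are still collected.

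The preceding sentence of the same section deals with injuries separately: "In the event that an unintentional home injury occurs during the study period, participants will be instructed to contact the research team immediately". It does not make an injury a ground for termination.

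Section 2.10 (Ethical Consideration) has a different trigger, excessive emotional burden. If such a participant cannot go on with the programme, "the data collected up to that critical point will be retained" and the reasons for study withdrawal are documented.

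Section 2.9 (Data Analysis) promises an intention-to-treat analysis "including all randomized participants in their originally assigned groups, regardless of adherence or withdrawal". Missing data are filled by multiple imputation with fully conditional specification.

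Section 2.8.1 defines the primary outcome as the number of home injuries, counted at T1 and T2 over the month before each visit.

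**The concern.** The 4-week programme is over before T1. In the follow-up period little is left to stop except home exercise and the T1 and T2 assessments. Ending participation at that stage most naturally means ending outcome collection.

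The trigger can overlap with the outcome. The primary events include falls, burns, swallowing problems and heat illness, and a serious one is a change in clinical condition. A fall with a fracture would also put the participant outside the entry conditions of Section 2.2, which exclude people under treatment for a fracture. If such people leave, the missing counts tend to be the higher ones. Imputation that borrows from those who stayed would then give counts that are too low. In a trial of 54 people with sparse events, a few such losses are noticeable.

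**Working it through.** **Reading the sections together.** Section 2.12 stops participation, not just sessions, in both periods, and promises recovery and safety contact only. Section 2.10, for its own separate case, treats inability to continue the programme as withdrawal from the study. Neither section provides for continued outcome collection. Section 2.9 keeps withdrawn participants in the analysis, but their missing counts must come from imputation, which in standard use assumes missing at random.

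**Size.** The article gives no injury rate and no termination rate, so there is no stated figure to reproduce. All rates below are assumptions.

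- Monthly counts are Poisson with mean μ: 0.40 in control, 0.28 in intervention (true difference 0.12, ratio 0.70).
- A share q of participants with at least one injury lose their count and are imputed from the rest of their arm.
- Proportion with no injury: p0 = exp(−μ), which is 0.670 in control and 0.756 in intervention.
- Mean after loss: μ(1 − q) / [p0 + (1 − p0)(1 − q)].

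For q = 25%:

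- Control: 0.40 × 0.75 / (0.670 + 0.330 × 0.75) = 0.300 / 0.918 = 0.327.
- Intervention: 0.28 × 0.75 / (0.756 + 0.244 × 0.75) = 0.210 / 0.939 = 0.224.

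| q, same in both arms | Control | Intervention | Difference | Ratio |
|---|---|---|---|---|
| 0 | 0.400 | 0.280 | 0.120 | 0.70 |
| 5% | 0.386 | 0.269 | 0.117 | 0.70 |
| 10% | 0.372 | 0.258 | 0.114 | 0.69 |
| 25% | 0.327 | 0.224 | 0.103 | 0.68 |

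In people: with 27 per arm, about 27 × 0.330 = 8.9 controls and 27 × 0.244 = 6.6 intervention participants would have an injury in a month. A 25% loss is then about two people per arm (2.2 and 1.6).

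**No true effect (0.40 in both arms).** Equal loss leaves the ratio at 1. Loss of 10% in one arm and 5% in the other gives 0.372 / 0.386 = 0.96, or 1.04 the other way round. Loss of 25% against 10% gives 0.327 / 0.372 = 0.88, or 1.14.

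**Second check, loss per injury.** If each injury independently leads to termination with probability q, and missing counts are left out without imputation, the retained mean is μ(1 − q). A simulation with an assumed control mean of 0.5 and a true ratio of 0.6 agrees: for q from 5% to 30% the ratio stays at about 0.60, while the difference falls from 0.20 to between 0.19 and 0.14. Missing counts run from 2.5% to 13.9% in control and from 1.5% to 8.6% in intervention.

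Both checks agree: equal selective loss lowers the counts and the absolute difference, hardly moves the ratio, and creates no effect where there is none.

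**The case against.** The strongest reply is that the triggering injury is probably on record already. Participants are told to report injuries at once, reported events go into a standard file (Section 2.12), injury logs are reviewed regularly (Section 4), and Table 2 marks the injury count during the intervention as well as at T0, T1 and T2. The arithmetic treats that count as wholly unknown, so it overstates the loss if the record is used. This stands in large part. But no text says that a reported injury enters the primary count of someone whose participation has ended, and later injuries in that person would still be missed.

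A second reply is that unequal loss is speculative. Sessions are twice weekly in one arm and once weekly in the other, which might lead to unequal detection. However, Section 2.7 says that both arms were monitored at similar intervals, and participants in both arms report their own injuries. This also stands: neither the direction nor the existence of a difference between arms can be established.

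A third is that losing 25% of the injured is extreme when any cut or collision counts. That is fair, and it is why the table starts at 5%.

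A reader might also infer three stronger points that the article does not support:

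- That only data up to termination are kept after a clinical change. The retention sentence in Section 2.10 concerns emotional burden, and it promises to keep data without barring later collection.
- That any change in condition, or a home injury as such, leads to termination. The change must meet the criteria, and an injury is not named among them.
- That Section 2.9 is contradicted. It foresees withdrawals and imputes their data.

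**Conclusion.** The point holds as a gap between the discontinuation wording and the intention-to-treat aim. Followed as written, Section 2.12 can remove T1 and T2 primary counts for reasons related to injury, and imputation under missing at random would not fully restore them.

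Under the assumed rates, equal loss of 5% to 25% of the injured shrinks the mean difference by roughly 2% to 14%, with almost no change in the ratio. Bias under no true effect arises only if loss differs by arm, for which the article gives no evidence. The result rests on three assumptions: that a serious home injury could meet the unstated criteria, that outcome collection stops with participation, and that the recorded injury is not otherwise used. The true size cannot be determined from the article. The case for changing the text is that the remedy is cheap, not that a large bias has been shown.

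**What to change.** Leave the discontinuation criteria as they are. In Sections 2.10 and 2.12, state that:

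- discontinuation stops the programme but not outcome collection;
- T1 and T2 injury counts and questionnaires are still collected, by telephone if needed, unless the participant withdraws consent for follow-up;
- the injury that led to discontinuation, already reported to the team, counts in the primary outcome.

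The cost is a change to the protocol and consent wording and a few extra telephone contacts.

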### 2.13. Patient and Public Involvement

An expert panel participated in the development, evaluation, and refinement of the injury prevention program. Facility managers at senior welfare centers will assist with participant recruitment, measurements, and program operation planning.

### 2.14. Expected Results

The SHIPs intervention is expected to produce measurable positive improvements among community-dwelling older adults. Following the intervention, participants are anticipated to experience a reduction in the number of home injuries, an increase in awareness of injury risks, and greater engagement in preventive behaviors. Their beliefs about home safety and injury prevention are also expected to be strengthened. Furthermore, the intervention is expected to contribute to improvements in physical functioning, psychological health, and overall health-related quality of life. Continuous support and monitoring throughout the intervention period are expected to promote program adherence, verify its effectiveness, and minimize the risk of unplanned dropouts or accidents. These expected outcomes align with the theoretical framework of this study and are supported by previous evidence suggesting that injury-prevention education interventions for older adults can yield synergistic benefits [22,34].

